## Abstract

**Background:**

Swine origin influenza A/H1N1 infection (H1N1) emerged in early 2009 and rapidly spread to humans. For most infected individuals, symptoms were mild and self-limited; however, a small number developed a more severe clinical syndrome characterized by profound respiratory failure with hospital mortality ranging from 10 to 30%. While supportive care and neuraminidase inhibitors are the main treatment for influenza, data from observational and interventional studies suggest that the course of influenza can be favorably influenced by agents not classically considered as influenza treatments. Multiple observational studies have suggested that HMGCoA reductase inhibitors (statins) can exert a class effect in attenuating inflammation. The Collaborative H1N1 Adjuvant Treatment (CHAT) Pilot Trial sought to investigate the feasibility of conducting a trial during a global pandemic in critically ill patients with H1N1 with the goal of informing the design of a larger trial powered to determine impact of statins on important outcomes.

**Methods/Design:**

A multi-national, pilot randomized controlled trial (RCT) of once daily enteral rosuvastatin versus matched placebo administered for 14 days for the treatment of critically ill patients with suspected, probable or confirmed H1N1 infection. We propose to randomize 80 critically ill adults with a moderate to high index of suspicion for H1N1 infection who require mechanical ventilation and have received antiviral therapy for ≤ 72 hours. Site investigators, research coordinators and clinical pharmacists will be blinded to treatment assignment. Only research pharmacy staff will be aware of treatment assignment. We propose several approaches to informed consent including a priori consent from the substitute decision maker (SDM), waived and deferred consent. The primary outcome of the CHAT trial is the proportion of eligible patients enrolled in the study. Secondary outcomes will evaluate adherence to medication administration regimens, the proportion of primary and secondary endpoints collected, the number of patients receiving open-label statins, consent withdrawals and the effect of approved consent models on recruitment rates.

**Discussion:**

Several aspects of study design including the need to include central randomization, preserve allocation concealment, ensure study blinding compare to a matched placebo and the use novel consent models pose challenges to investigators conducting pandemic research. Moreover, study implementation requires that trial design be pragmatic and initiated in a short time period amidst uncertainty regarding the scope and duration of the pandemic.

**Trial Registration Number:**

ISRCTN45190901

## Background

### Influenza and Swine Origin Influenza A/H1N1 Infection (H1N1)

On June 11, 2009, the World Health Organization (WHO) declared that infection with the Swine Origin Influenza A/H1N1 virus had reached pandemic proportions [1]. Cases were recorded in more than 180 countries and outbreaks that strained national resource capacities were documented in Canada, Australia, Chile, Argentina, and elsewhere.

Throughout history, pandemic influenza has posed a recurrent threat to human populations. Seasonal influenza is responsible for more than 50,000 deaths per year in the United States [2]. The capacity of the influenza virus to mutate and spread from animals to humans has resulted in intermittent pandemics. The 1918 pandemic was the largest in recent history and caused between 40 and 50 million deaths worldwide [3]. Smaller pandemics in 1957 and 1968 were associated with mortality spikes but their effects were mild at the population level [4]. Experts believe further pandemics will certainly occur, but are uncertain about when. Several years ago, the avian H5N1 influenza virus threatened to be the vector of the next pandemic. While highly virulent when transmitted from infected chickens to humans, the absence of human-to-human transmission resulted in a small number of cases worldwide [5].

In early 2009, a novel strain of influenza, swine origin influenza A/H1N1 infection (H1N1) emerged in swine and rapidly spread to humans [6]. Originating in Mexico, the strain proved highly infectious and was spread by person-to-person contact with a predilection for younger hosts. While early epidemiologic data suggested that although H1N1 was highly infectious, it was less virulent [7,8] than anticipated with a case fatality rate of approximately 0.5% of infected individuals. For the majority of infected individuals, symptoms were mild and self-limited; however, a small percentage of infected individuals developed profound respiratory failure requiring extraordinary means of oxygenation support including high frequency oscillation (HFO) ventilation and extracorporeal membrane oxygenation (ECMO) [9]. Caring for the most severely ill patients during a pandemic results in an increased need for intensive care unit (ICU) resources and strains available personnel and equipment. There is little excess capacity to care for critically ill patients in most developed countries, and minimal capacity in developing countries.

### Rationale for Study Intervention

Supportive care and antiviral agents, especially neuraminidase inhibitors (such as oseltamivir and zanamivir), are the mainstay of treatment for influenza. While efficacious in reducing viral load and abating symptoms in ambulatory patients, their effects on outcomes in critically ill patients have not been established. Their utility in treating severe pandemic H1N1 influenza may be compromised by widespread use and emergence of viral resistance [10,11], limited supplies, policies regarding treatment strategies, and cost and availability, especially in developing countries [12]. Human and animal data suggest that the course of influenza may be favorably influenced by certain agents not classically considered as treatments for influenza [13-16] that are comparatively inexpensive and readily available. Such agents may provide independent benefit in treating viral infection and are attractive as adjuvant treatments.

### Statin Therapy for Influenza

Statins lower plasma lipid levels by inhibiting HMG CoA reductase, the enzyme responsible for converting HMG CoA to mevalonate, a rate-limiting step in cholesterol biosynthesis. Multiple observational studies have suggested that statins may be of benefit in patients with a variety of severe infections [17-22] by exerting an effect in attenuating inflammation [23,24]. The mechanism of this activity is uncertain but may involve their ability to restrict cholesterol availability in cell membranes of the innate immune system. Cholesterol is a key component of lipid rafts, membrane-associated microdomains that support cell signaling in response to exogenous inflammatory stimuli. Raft disruption may attenuate the cellular response to inflammatory stimuli [25,26].

Experimental studies show that pre-treatment with statins attenuates the severity of acute lung injury (ALI) following intestinal ischemia-reperfusion [27] and the inflammatory response to intravenous lipopolysaccharide challenge in human volunteers [28]. The combination of a statin and caffeine inhibits viral replication and attenuates lung injury in murine influenza models [29]. Population-based studies suggest that statins are associated with reduced inflammatory morbidity in critically ill patients receiving them [20] and reduced mortality in patients with influenza and chronic obstructive pulmonary disease (COPD) patients [30]. Reviewing 3,921 hospitalized patients with laboratory confirmed influenza, of whom 1,019 were receiving a statin at the time of admission, Vandermeer and colleagues found that statin use was independently associated with a reduced risk of death (adjusted OR = 0.34, 95% CI: 0.16-0.70) in a multivariable logistic regression model [31]. The benefits of statins appear to be best established in patients receiving them prior to the onset of infection. Cohort studies report conflicting results on the ability of statins to attenuate organ dysfunction with Schmidt and colleagues finding that statins reduce mortality in critically ill patients with multiple organ dysfunction syndrome [32] and Kor et al reporting that statin use was not beneficial in resolving organ dysfunction [33].

### Rosuvastatin: Risks and Benefits

Statins are widely used and well-tolerated medications. Rosuvastatin differs from other HMG CoA reductase inhibitors in that only up to 10% of the parent compound is metabolized by cytochrome P450 2C9 and 2C19 and not by P450 3A4 [34]. As a result, it exhibits fewer drug-drug interactions, and serum concentrations are not affected by CYP2D6 gene polymorphism. Adverse events seen with rosuvastatin are generally mild and may include muscle symptoms, however, myopathy and rhabdomyolysis occur infrequently in patients taking 40 mg/day or less. As with other HMG-CoA reductase inhibitors, a dose-related increase in liver transaminases and creatinine kinase (CK) has been observed in small numbers of patients taking rosuvastatin. The overall occurrence of clinically significant transaminase increases is low (< 1%) and similar across rosuvastatin doses ranging from 5 mg/day to 40 mg/day [35]. Patients with severe liver disease may have increased exposure to rosuvastatin [35].

### Study Objective

The International Forum of Acute Care Trialists (InFACT) is an informal alliance of investigator-led clinical trials networks whose remit is to improve the care of critically ill patients through the promotion of scientifically rigorous clinical research. Based on our preliminary understanding of H1N1 influenza, members of the Canadian Critical Care Trials Group (CCCTG), working in collaboration with members of InFACT, designed the Collaborative H1N1 Adjuvant Treatment (CHAT) Pilot Trial to investigate the feasibility of conducting an international therapeutic trial during a global pandemic and the potential for adjuvant rosuvastatin, in addition to standard treatment, to influence clinical outcomes in influenza A (H1N1) associated critical illness.

## Methods

### Study Design

A multi-national feasibility RCT involving adult ICUs in Canada, Saudi Arabia, Mexico, Argentina Australia/New Zealand. An overview of the study design is provided in Figure 1 (**see **Figure 1).

**Figure 1 F1:**
[figure not shown]
**Study Overview**.

### Primary Objective

[1] The ability to recruit the desired patient population under pandemic conditions (i.e., the proportion of eligible patients enrolled in the CHAT Pilot Trial).

### Secondary Objectives

[2] Adherence to the medication administration regimen as outlined in the study protocol.

[3] The ability to collect the required primary and secondary endpoints for the planned full CHAT trial.

[4] The number of patients who receive open-label statins.

[5] The number of consent withdrawals.

[6] The impact of approved consent models on recruitment rates.

### Patient Screening

A dedicated research coordinator will screen patients for eligibility on a daily basis in the ICUs at participating sites. If the study inclusion criteria are fulfilled and no exclusion criteria are present, the research coordinator will identify the patient as a potential study participant. The attending physician or intensivist will confirm eligibility for participation in the CHAT Pilot RCT.

### Inclusion Criteria

Criteria to identify potential candidates for study inclusion will include:

1) Critically ill adult patients ≥ 16 years of age admitted to an adult ICU for any reason with suspected, probable or confirmed novel swine origin influenza A/H1N1 infection (**see **Additional File 1).

2) Requiring mechanical ventilation (invasive or non-invasive)

3) Receiving antiviral therapy (any medication at any dose and for any intended duration) for ≤ 72 hours

4) Attending physician or intensivist must have a 'moderate' to 'high' index of suspicion for H1N1.

### Exclusion Criteria

1) Age < 16 years

2) Do not resuscitate or re-intubate order documented on chart or anticipated withdrawal of life support

3) Weight < 40 kg

4) Unable to receive or unlikely to absorb enteral study drug (e.g., incomplete or complete bowel obstruction, intestinal ischemia, infarction, short bowel syndrome)

5) Rosuvastatin specific exclusions:

a. Already receiving a statin

b. Allergy or intolerance to statins.

c. Receiving niacin, fenofibrate, cyclosporine, gemfibrozil, any protease inhibitor (including but not limited to lopinavir and ritonavir) or planned use of oral contraceptives or estrogen therapy during the ICU stay.

d. CK exceeds 5,000 U/L **or **ALT exceeds 8 times the upper limit of normal (ULN).

6) Severe chronic liver disease (Child-Pugh Score 11-15) (**see **Additional File 2)

7) Previous enrolment in this trial

8) Pregnancy or breast feeding

9) At the time of enrolment, receipt of > 72 hours of antiviral therapy.

10) Known or suspected clinically significant myositis or myopathy.

### Eligible, Non-Randomized Patients

We will record reasons why eligible patients are not randomized into the CHAT Pilot Trial under the following categories:

a) Substitute Decision Maker (SDM) consent refusal

b) Physician refusal of consent

c) SDM not available to provide consent and waived/deferred consent not permitted

d) SDM does not exist and waived/deferred consent not permitted

e) Coordinator workload

f) Coordinator not available during eligible time-window

g) Enrolment in a competing trial

h) Other (specification required)

To enhance trial feasibility and given the need to conduct a pragmatic trial, co-enrolment in other prospective observational studies or RCTs (not investigating similar or alternative H1N1 treatments) in operation in the ICU setting will be permitted and recorded in sites where permitted by the local Research Ethics Boards (REBs) [36].

### Study Randomization

To preserve allocation concealment, participants will be randomized centrally. Randomization lists will be distributed by the study methods centre to the research pharmacies of participating centres. Stratified variable block randomization, based on centre alone, will be performed to take into consideration differences in patient characteristics at participating ICUs. Day one will be considered the day of study treatment initiation, which may or may not be the same day of randomization.

### Consent

A waiver of consent is the preferred option for participant enrollment given the context of a global pandemic. We have constructed a consent algorithm to direct the consent process at sites where the local REB has not approved a waiver of consent (**see **Additional File 3). In this trial, we will request that patients be enrolled in the study, and consent be deferred to SDMs or to the patient (whomever is able to provide consent first), when it is not possible to obtain consent within 24 hours. Consent may be obtained in person or by telephone as per local practices. In the event that patients die before providing consent, we request permission from REBs to include data collected during study participation.

### Study Treatment Overview

Using randomization lists provided by the study methods centre, research pharmacists will assign critically ill adults to once daily enteral administration of rosuvastatin or matched placebo for 14 days. Only the research pharmacy staff will be aware of the assigned treatment arm. The site investigators, research coordinator, clinical pharmacist involved in the care of the patient and all other study personnel will remain blinded to treatment assignment. An oral placebo for nasogastric administration, identical in appearance (colour and consistency matched) to crushed rosuvastatin, will be prepared by Pharmacy 1 (Toronto, Canada) and supplied to the study sites. All other aspects of patient management will be left to clinician discretion as per pragmatic trial design. The Applied Health Research Centre of the Keenan Research Centre and Li Ka Shing Knowledge Institute (St Michael's Hospital, Toronto, Ontario) will be the Study Methods Centre.

### Study Drug Administration

#### Delivery Route

Study drug will be administered once daily through an enteral feeding tube or orally if the patient is able to safely take oral medications. The type and placement of the enteral feeding tube (nasogastric, nasoenteric, percutaneous endoscopic gastrostomy, orogastric, oroenteric, etc.) will be at the discretion of the attending clinical team. The ability to safely take oral medications will be determined by the patient's primary care team.

#### Initial Dose

The first study drug dose (rosuvastatin or placebo) will be administered within 4 hours of randomization as a loading dose of 40 mg unless the subject is of Asian (Chinese, Korean, Japanese, Phillipino, Vietnamese, or Asian-Indian) descent, age <18 years or has serum creatinine greater than or equal to 248 umol/L (2.8 mg/dL) (see requirements for dose adjustments below).

#### Subsequent Doses

Thereafter doses of 20 mg will be administered at 22:00 hrs daily (+/- 4 hours) starting on the next calendar day (study day 2) as a maintenance dose. If the patient is of Asian descent, is <18 years, or serum creatinine is greater than or equal to 248 umol/L (2.8 mg/dL) dose adjustments will be required according to the dose adjustment algorithm (see requirements for dose adjustments below). Dose adjustment is only necessary for patients with renal impairment and not receiving dialysis. Once dialysis is started and serum creatinine remains elevated, dose adjustment is not required.

#### Missed Doses

If for any reason a maintenance dose is not administered at the intended time, it may be administered subsequently but not more than 12 hours after the intended time of administration. If greater than 12 hours has elapsed since the last scheduled dose, the patient will receive another loading dose, and then maintenance dosing will resume on the next calendar day as outlined above. A missed dose, for reasons other than outlined under medication discontinuation will be considered a protocol violation.

#### Dose Adjustments

The loading (40 mg) and daily maintenance (20 mg) doses will be reduced by 50% for patients:

a) who have at least one parent of Asian descent (loading 20 mg and daily 10 mg),

b) whose age < 18 years (loading 20 mg and daily 10 mg),

c) whose serum creatinine concentration is greater than or equal to 248 umol/L (2.8 mg/dL) who are not on renal replacement therapy (loading 20 mg and daily 10 mg), and by 75% for patients:

d) who have at least one parent of Asian descent and/or age < 18 years *and *serum creatinine is greater than or equal to 248 umol/L (2.8 mg/dL) (loading 10 mg and daily 5 mg).

#### Concomitant Medication Administration

Intermittent oral antacids should be administered no closer than 6 hours before or after administering rosuvastatin to avoid influencing study drug absorption [37]

#### Duration of Treatment

Given the substantial potential for false negative influenza results, we will continue adjuvant treatment administration, regardless of H1N1 testing results (positive or negative), for 14 days or until a criterion for cessation is met. If patients are liberated from mechanical ventilation (invasive or non-invasive) and discharged from the ICU between days 1 and 9 they will be advanced to day 10 of study drug administration. In the event that patients remain in the ICU for observation (e.g., possible reintubation or initiation of non-invasive ventilation) then study drug administration will NOT be advanced to day 10 until they are discharged.

### Completion of Study Drug Administration

Study drug administration will be stopped when one of the following conditions is met, whichever comes first:

1. 14 days after randomization

2. Hospital discharge (including transfer to an alternate care facility)

3. Death

4. CK noted to exceed 5,000 U/L (in the absence of an alternative diagnosis) or patient is determined to have clinical myositis or myopathy (at the discretion of the primary care team, patient may be re-challenged with study drug if CK or clinical findings no longer meet this criterion).

5. Alanine aminotransferase (ALT) exceeds 8 times the ULN (in the absence of an alternative diagnosis)

6. Co-administration of any of the following: niacin, fenofibrate, cyclosporine, gemfibrozil, lopinavir, ritonavir, oral contraceptives or estrogen

7. Attending physician or intensivist or SDM request to stop treatment.

We will request for data collection to continue in patients withdrawn from therapy prematurely. Clinicians will be encouraged to continue study medication despite negative H1N1 testing due to the potential for false negative results and the potential role for an anti-inflammatory agent (rosuvastatin) in severe lung disease. Decisions regarding continuation or discontinuation of antiviral treatment will be left to the discretion of the attending physician or intensivist.

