### Follow-Up

Research staff will assess participants daily for adverse effects for the duration of treatment. CHAT study participants will have daily CK and liver function [aspartate aminotransferase (AST) and ALT] levels collected as part of the study protocol. Study drug will be discontinued if hypersensitivity is suspected (see Criterion 7 Completion of Study Drug Administration).

We will record the number of patients receiving full treatment and reasons for the inability to complete the assigned treatment duration (i.e., death, transfer to an alternate care facility, study withdrawal, etc). The study Data Safety and Monitoring Board (DSMB) will review all patients withdrawn from the study, safety data, and deaths.

All patients will be followed until death or hospital discharge. We will record the vital status of all patients at 90 days and hospital discharge, whichever occurs first. At day 60 patients remaining on the ventilator will be deemed ventilator dependent. Randomized patients will be considered successfully extubated when they remain off positive pressure ventilation (invasive or non-invasive ventilation) for 48 consecutive hours. If patients are re-intubated *within *48 hrs following extubation, they will be followed until they achieve one of the aforementioned outcomes. Patients discharged from the ICU and requiring readmission and re-initiation of mechanical ventilation (invasive or non-invasive) will be treated according to usual practice and will not be randomized on a second occasion to this study.

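### Stopping criterion 6 names only two protease inhibitors while exclusion 5c bars the whole class, so a newly started regimen with neither drug triggers no mandatory stop

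*Protocol article*

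**What the plan says.** Exclusion 5c, one of the rosuvastatin-specific exclusions in the protocol article, bars patients receiving niacin, fenofibrate, cyclosporine, gemfibrozil or "any protease inhibitor (including but not limited to lopinavir and ritonavir", and patients with "planned use of oral contraceptives or estrogen therapy during the ICU stay".

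Under Duration of Treatment, study drug continues "for 14 days or until a criterion for cessation is met". The criteria are listed under Completion of Study Drug Administration and are mandatory: meeting any one of them stops study drug. Criterion 6 is "Co-administration of any of the following: niacin, fenofibrate, cyclosporine, gemfibrozil, lopinavir, ritonavir, oral contraceptives or estrogen". Criterion 7 is "Attending physician or intensivist or SDM request to stop treatment".

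**The concern.** The entry rule treats the protease inhibitor class as incompatible with study drug. The on-treatment rule covers the same co-medications but narrows the class to two named drugs and gives no reason. If both rules are followed as printed, a co-medication that would have kept a patient out of the trial can be added after randomization without obliging anyone to stop study drug.

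What is at stake is the consistency of a patient-safety rule. The sample size, the primary feasibility outcome and the planned analysis are not involved.

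**Working it through.** No arithmetic underlies this point. The check sets the two lists side by side and then looks for any other rule that closes the gap.

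**Step 1: compare the lists.**

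| Co-medication | Exclusion 5c | Stopping criterion 6 |
|---|---|---|
| Niacin | yes | yes |
| Fenofibrate | yes | yes |
| Cyclosporine | yes | yes |
| Gemfibrozil | yes | yes |
| Oral contraceptives | yes, if planned | yes |
| Estrogen | yes, if planned | yes |
| Protease inhibitors | whole class, two drugs as examples | lopinavir and ritonavir only |

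Six of the seven entries match and appear in the same order. Only the seventh is narrowed.

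**Step 2: does the entry rule already prevent the situation?** No. In 5c the planned-use condition is attached only to oral contraceptives and estrogen. For protease inhibitors the rule covers drugs being received at entry, so a later start is not excluded.

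**Step 3: does another section restrict protease inhibitors during treatment?**
- Concomitant Medication Administration deals only with antacids: "Intermittent oral antacids should be administered no closer than 6 hours before or after administering rosuvastatin".
- Study Co-interventions has additional antiviral treatments recorded and does not restrict them.
- Completion of Study Drug Administration leaves decisions on continuing or stopping antivirals to the clinician.
- Duration of Treatment shortens the course after ICU discharge but does not end it. Patients off ventilation and "discharged from the ICU between days 1 and 9 they will be advanced to day 10 of study drug administration", so days 10 to 14 remain, which is at most 14 - 10 + 1 = 5 daily doses.

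**Step 4: which stops remain for such a patient before day 14?**
- Criteria 2 and 3: hospital discharge or death.
- Criterion 4: CK above 5,000 U/L without another explanation, or clinical myositis or myopathy at any CK level.
- Criterion 5: ALT above 8 times the upper limit of normal without another explanation.
- Criterion 7: a request to stop.

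None of these is triggered by the co-medication itself. Criteria 4 and 5 need a clinical or laboratory event to occur first. They are supported by daily monitoring under Follow-Up ("CHAT study participants will have daily CK and liver function" tests). Criterion 7 depends on someone recognising the issue and asking.

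**Step 5: who is affected?** Patients already on any protease inhibitor are excluded at entry. A regimen containing lopinavir or ritonavir, alone or with another protease inhibitor, triggers criterion 6 as written. What is left is a patient newly started, within a course of at most 14 days, on a regimen containing neither drug.

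**The case against.** The case for leaving the text alone has four parts.

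**Stopping rules need not mirror entry rules.** Exclusion 5d bars patients on CK or ALT outright, whereas criteria 4 and 5 make allowance for another diagnosis and criterion 4 permits re-challenge. Current statin use is an exclusion (5a), yet statins are absent from criterion 6. This stands as a reason not to assume a slip, and the shorter list may be deliberate. It does not explain why a list that otherwise repeats 5c entry for entry departs from it at one entry without comment.

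**Criterion 7 is the catch-all.** Follow-Up sends suspected hypersensitivity to criterion 7, so the protocol does use it for safety stops that are not itemised. That is fair, and a patient is not locked into treatment. But for hypersensitivity the article states that study drug will be discontinued. It makes no such statement for other protease inhibitors, so for them the stop stays discretionary.

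**The safeguards are substantial.** A reader might infer that the only mandatory safety stops left are the CK and ALT limits. The text does not support this, because criterion 4 also stops study drug for clinical myositis or myopathy whatever the CK. Staff also assess patients daily for adverse effects.

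**Harm is not shown.** A reader might infer that continued dosing with another protease inhibitor is known to be dangerous. The article describes no such interaction. Its section on the risks and benefits of rosuvastatin says the drug is not metabolised by P450 3A4 and has fewer interactions than other statins. The only support is the article's own decision to bar the class at entry. This part stands and limits the point to consistency.

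It might also be said that an article condenses the full protocol. That would excuse an omission. Here both lists are printed, and they disagree.

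**Conclusion.** The mismatch is real. A protease inhibitor regimen containing neither lopinavir nor ritonavir is barred at entry, but if started during treatment it triggers no mandatory stop. Study drug would then end early only under criteria 2 to 5 or 7.

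The size is small. The number of such patients cannot be derived from the documents, and in a pilot of 80 patients it is probably low. Nor can the extra statin exposure per patient be bounded simply by counting the remaining maintenance doses. Missed Doses allows a further loading dose, some patients have reduced doses, half or so of the patients may be on placebo, and centres in Australia and New Zealand may use atorvastatin.

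The conclusion assumes that criterion 6 is read as the closed list it is printed as, and that 5c expresses the intended scope of the concern about protease inhibitors. If the narrower list was intended, only its reason is missing. The point does not extend to the primary feasibility outcome or to the sample size. Severity is low: a safety-consistency correction.

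**What to change.** In stopping criterion 6, replace the two drug names with the class wording of exclusion 5c, that is "any protease inhibitor (including but not limited to lopinavir and ritonavir" with the bracket closed, and leave the other entries as they are. If the narrower list is deliberate, keep it and give the reason in one sentence.

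The cost is one line of text and a short notice to sites. No extra patients, visits, tests or analyses are needed. A side benefit is that a stop made for this reason would fall under an explicit criterion. It would then not depend on a recorded criterion 7 request to avoid being classed as a missed-dose violation or counted against the 10% limit on doses not given.
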